
### Data collection

Data is collected through two rounds of household surveys in each village on a rolling basis. As shown in Fig 3, the baseline survey is conducted in each village before villages are randomly assigned to the intervention and the control groups. Second, the endline survey is conducted after the end of the interventions to measure intervention impacts, which are measured using selected outcome variables. The endline survey has two components: participant endline survey and community endline survey (Fig 3). The former is conducted with the 15 participants (household heads) who take part in the interventions (Treatment P or Treatment PC) in each village. The latter is conducted with the remaining 15 household heads who participated in the baseline surveys but were not selected to participate in the interventions. Since no intervention is implemented in the control arm, all the 30 household heads who participated in the baseline surveys are included in the community endline survey for the villages allocated to this arm. Training is given to field data collectors (*survey team*) responsible for baseline and endline surveys. They are trained on the content of questionnaires, question-asking techniques and cultural sensitivity [43]. Supervisors are responsible for quality control in the field and addressing issues arising during data collection. Data collectors involved in baseline surveys are blinded in such a way that they are instructed not to share any information in the villages regarding the randomization of the villages into the intervention or control group. This is important to ensure that their interactions and communication with the villages do not unintentionally disclose any information about the intervention that could influence its later implementation.

#### Data source and data collection method

The data sources and collection methods are summarized in Table 4, developed and adapted based on Wendt, Sparling [43]. A questionnaire is developed to collect data during baseline and endline surveys. The baseline and endline surveys are made similar across countries but modified slightly to reflect differences between the local contexts. The endline survey follows the same structure as the baseline survey, except that it will be redesigned to ensure that the participants’ experiences regarding insect farming and consumption during the intervention are fully captured. The questionnaires have several sections, including socioeconomic and demographic status, child and household dietary diversity, insect farming and consumption knowledge, food insecurity perception, perceived benefits and risk attitude, and willingness to adopt insect farming and consumption. In addition to the baseline and endline surveys, data will be collected through intervention output monitoring while the intervention is being conducted (see Table 5).

**Table 5 pone.0288870.t005:** Data source and data collection method.

Activity	Data source	Data collection device	Responsible team	Population	Frequency
**Survey**	Baseline survey	Smartphone	Survey team	Treatment and control groups	Once per village
**Survey**	Endline survey	Smartphone	Survey team	Treatment and control groups	Once per village
**Monitoring**	Intervention activity records	Smartphone	Implementation team	Treatment groups only	After every intervention activity
**Monitoring**	Output monitoring	Smartphone	Implementation team	Treatment groups only	Bi-monthly in each village on a rolling basis

Note: table adapted from Wendt, Sparling [43]

#### Data management

Redcap (https://www.project-redcap.org/) is used to manage all data in the project. Data collection instruments are created using the same software, which allows detection and prevention of common data collection errors. It also enables storage and compilation of data as it comes in from the field. The research team and field supervisors are responsible for regular data quality checks. Any events of data concerns are communicated with the survey team and field supervisors for resolution. Access to data is restricted to principal investigators and the server where the data are stored is password protected to ensure confidentiality.

### Analysis plan

We focus on the intent-to-treat (ITT) effects. Some participants may not attend to the agricultural training or nutrition education sessions despite being invited to the sessions. In the ITT analysis, we estimate the effects of the interventions by including all participants irrespective of whether they participated in the interventions or not. Our basic regression framework to estimate the ITT effect is:

$$Y_{i}=\beta_{0}+\beta_{1}T_{1}+\beta_{2}T_{2}+\varepsilon_{i}$$
(1)

*Y_i_* is the outcome variable for individual *i*, *T*_1_ and *T*_2_ are dummy variables which take the value 1 depending on which intervention the household in a village was assigned, 0 otherwise. The random error term is represented by *ε_i_*. The impacts of the interventions are given by *β*_1_ and *β*_2_. Standard errors are clustered at the village level to account for within village correlations. We conduct further analyses by extending Eq (1) to account for vectors of individual characteristics and other control variables, baseline and endline data, and treatment heterogeneity in terms of differences in the effects of the two interventions–*Treatment P* and *Treatment PC*. We assess any spillover effects by interviewing households who did not participate in the intervention. This assists in understanding whether and how the information regarding insect farming and consumption spread beyond the targeted households in the intervention [37].

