**Method:**

The study is designed as a multi-site randomized controlled trial to evaluate the impacts of agricultural training alone or in combination with nutrition education on the adoption of insect farming in Ghana, Kenya and Uganda. In each of the three countries, ninety-nine villages are randomly assigned to one of three arms: two intervention arms and a control arm with no interventions. Focusing on production (P), the first intervention arm covers agricultural training on insect farming combined with provision of insect production starter kits. Focusing on both production and consumption (PC), the second intervention arm involves the same intervention components as treatment P plus additional nutrition education. The impacts of the interventions are measured by comparing baseline and endline data collected one year apart. Primary outcomes are adoption of insect farming and consumption of the farmed insects.

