### Sample size

To calculate the sample size, we determine the minimum detectable effect size based on the best available data in the literature regarding the effects of educational programs on adoption of insect farming. In Ghana, Kenya and Uganda, insect farming remains relatively uncommon compared to other types of farming activities. For instance, in a pilot study on cricket (*Scapsipedus icipe*, *Acheta domesticus)* farming in Kenya, only 12% of the sampled farmers adopted cricket farming [28]. We use this information to determine the minimum detectable effect size in our power analysis. We assume a minimum detectable effect size of 0.25 for Kenya, as an effect size of 0.12 would be too small to be detected given the available budget for the study. In Ghana, 560 farmers were trained as part of a pilot project focusing on farming Palm Weevil (*Rhynchophorus phoenicis*) production near their homes or gardens [34]. The same study reported that 48% of the trained farmers were actively farming Palm Weevil after the training. To avoid overestimation of the effect size, we consider a minimum detectable effect size of 0.25 for Ghana. In Uganda, pilot studies indicating the proportion of farmers involved in the farming of African bush crickets (*Ruspolia differens Serville*) were not found. Thus, we refer to related studies on the adoption of climate-smart agriculture practices in Uganda. Accordingly, we assume a minimum detectable effect size of 0.25 based on a previous study concerning climate-smart agricultural interventions [35].

Using the Optimal Design Software for multilevel and longitudinal research [36], the sample size is calculated based on a 0.8 power, 0.05 significance level and 0.06 intra-cluster correlation coefficient. Fig 2 shows that a total of 64 clusters (villages), each with 15 participants, are needed to obtain 80% of power for cluster randomized designs with two intervention groups. The minimum sample size across each of the intervention and control arms thus includes 32 villages in each country. To ensure that we detect the same effect size or smaller, we increase the sample size to 33 villages for each of the intervention and control arms.

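### Eq (1) has no country term although villages are randomised within country; a pooled fit as written is unbiased, but its standard errors are too large and power for PC versus P is lost

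*Protocol article*

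**What the plan says.** Country is a randomisation stratum. The abstract states: "In each of the three countries, ninety-nine villages are randomly assigned to one of three arms". The Sample size section fixes the split: "we increase the sample size to 33 villages for each of the intervention and control arms". It also sizes each country on its own: "The minimum sample size across each of the intervention and control arms thus includes 32 villages in each country".

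Under Recruitment and randomization, a lottery in each treated village then picks 15 of the 30 baseline households for the intervention. The other 15 stay in the community endline survey, as do all 30 households in control villages.

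Eq (1) in the Analysis plan regresses the outcome on T1 and T2 alone, with standard errors clustered by village. The indicators are "dummy variables which take the value 1 depending on which intervention the household in a village was assigned, 0 otherwise". Further control variables, and the comparison of the two interventions, come only in later extensions of Eq (1), and country is not named there. Spillover is covered by one sentence on method: "We assess any spillover effects by interviewing households who did not participate in the intervention".

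**The concern.** An analysis should reflect the strata within which units were randomised. The countries differ in insect species, starter kit and expected uptake. The protocol's own sources report 12% adoption in a Kenyan pilot, while in Ghana "48% of the trained farmers were actively farming Palm Weevil after the training". If the three countries are pooled without a country term, those differences sit in the village-level residual and inflate the clustered standard error, although the balanced design has already removed them from the treatment contrast. Most exposed is PC versus P, the contrast that isolates the added nutrition education and where a modest difference is plausible.

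A second, smaller matter is that the definition of T1 and T2 does not say outright where the lottery-unselected households in treated villages belong.

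**Working it through.** **1. The plan's own figure.** The inputs are in the Sample size section: "the sample size is calculated based on a 0.8 power, 0.05 significance level and 0.06 intra-cluster correlation coefficient", with 15 households per village and an effect size of 0.25, read here as a standardised difference with a two-sided test. For J villages in two arms the noncentrality is λ = J·d²/[4(ρ + (1−ρ)/n)].
- ρ + (1−ρ)/n = 0.06 + 0.94/15 = 0.1227
- λ = 64 × 0.0625/(4 × 0.1227) = 8.15, and F(1, 62) gives power 0.803

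Sixty-four is the smallest even number of villages reaching 0.80. The figure is reproduced, and it is a per-country figure.

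**2. Pooled fit, PC versus P.** Assumptions: adoption in P of 12%, 25% (Uganda, assumed) and 48%; ICC 0.06; 15 households per treated village; 99 villages per arm over three countries.
- Mean p(1−p) = (0.1056 + 0.1875 + 0.2496)/3 = 0.1809
- Village-mean variance within country = 0.1809 × 0.1227 = 0.0222
- Variance of the three country rates around their mean of 0.2833 = 0.0222
- True standard error with no PC–P difference = √(2 × 0.0222/99) = 0.0212
- Clustered standard error from Eq (1) = √(2 × (0.0222 + 0.0222)/99) = 0.0299
- Ratio = 1.41; rejection rate = 2[1 − Φ(1.96 × 1.41)] = 0.006

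**3. Power for a 6-point difference** (PC at 18%, 31%, 54%). For PC, mean p(1−p) = 0.2033 and village-mean variance = 0.0249. The true standard error is √((0.0222 + 0.0249)/99) = 0.0218.

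| Model | Reported SE | Power |
|---|---|---|
| Eq (1) as written | √((0.0222 + 0.0249 + 2 × 0.0222)/99) = 0.0304 | Φ((0.06 − 1.96 × 0.0304)/0.0218) = 0.51 |
| Country dummies | √((0.0222 + 0.0249 + 2 × 0.0055)/99) = 0.0242 | 0.72 |
| Centred country-by-arm terms | 0.0218 | 0.79 |

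Common country dummies recover only part of the loss. Control villages have almost no adoption in any country and hold half the households, so the fitted country effect is half the deviation seen in the treated arms. A quarter of the between-country variance remains (0.0222/4 = 0.0055). Beta-binomial simulations under the same assumptions agree: standard error 0.030 against a true SD of 0.021 to 0.022, rejection of 0.5% to 0.75% under no difference, and power of 49–55%, 69–73% and 77–81% for the three models.

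**4. Sensitivity to the country assumption.** If country explains 0, 5, 10 or 20% of outcome variance, the standard error is inflated by 1.00, 1.20, 1.38 or 1.74. Type I error is then about 0.050, 0.019, 0.007 or 0.001. Pooled power at 0.25 SD stays at 0.999, 0.996, 0.990 or 0.946; at 0.15 SD it is 0.85, 0.75, 0.62 or 0.34.

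**5. Unselected households.** Per country, with 33 villages per arm and a true effect of 0.25 SD in selected households. Spillover is assumed, as a share of that effect.

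| Coding of unselected households | Expected coefficient at spillover 0 / 25 / 50 / 100% |
|---|---|
| Left out | 0.25 throughout (power 0.86 with 30 controls per village) |
| Coded 1 by village | 0.125 / 0.156 / 0.188 / 0.25 (power 0.38 / 0.54 / 0.70 / 0.91) |
| Coded 0, merged with controls | 0.25 / 0.219 / 0.188 / 0.125 |

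**The case against.** The best defence is that the trial reads as three parallel country trials. Effect sizes are set by country, the village count is a per-country figure that reproduces, Table 1 is per country, and species and kits differ. Fitted by country, Eq (1) needs no country term. This stands as a plausible reading, but the Analysis plan does not state it, and the overall aim is framed for Africa as a whole.

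Even when pooled, the equal split prevents bias and the test errs on the safe side. The arm-versus-control effects that Eq (1) estimates directly are hardly at risk. On the inputs above, with 0.5% adoption assumed in controls, the effect is 0.283 − 0.005 = 0.278. Its inflated standard error is √((0.0222 + 0.0222 + 0.0005)/99) = 0.021, about 13 times smaller than the effect. PC versus P belongs to the extensions of Eq (1), where country could enter among the control variables. All of this stands. It limits the damage to lost precision, mainly for PC versus P. The 12% and 48% also come from separate pilots with different denominators, so they illustrate between-country variation in this trial and do not measure it.

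A reader might also infer that the dummies misplace the unselected households. The documents do not show that. The intention-to-treat paragraph concerns people invited who may not attend, and only lottery-selected households are invited. Data collection gives the others a separate community survey, and the Analysis plan puts non-participating households in the spillover assessment. The natural reading leaves them out of Eq (1). The opening for another reading is narrow: the Table 1 notes use participants for all 30 surveyed households and for the remaining 15, while Data collection uses the word for the 15 selected.

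**Conclusion.** The point holds in a conditional form. Eq (1) omits the randomisation stratum, and the protocol does not say that it is fitted by country. Fitted to pooled data as written, it gives unbiased estimates with standard errors about 40% too large for PC versus P, and power for a 6-point difference of about 51% where 72% to 79% is available from the same data. These sizes rest on adoption of 12/25/48% (25% assumed for Uganda) and an ICC of 0.06. The loss is smaller if country explains less of the variance, and absent in a per-country fit. The stronger inference, that Eq (1) yields biased effects or false positives, is not supported: the error is in the conservative direction.

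The place of the unselected households is a matter for clarification and not a demonstrated error. It is worth settling because village-level coding would halve the effect if there were no spillover, and merging with controls would dilute it if there were.

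**What to change.** State one of two options: fit Eq (1) separately in each country, or fit a pooled model with country fixed effects. In the pooled model, centred country-by-arm terms are optional but recover the precision that common dummies leave behind. Keep village-clustered standard errors in either case.

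Define T1 and T2 as 1 for lottery-selected households in P and PC villages respectively, with control-village households as the reference. Give unselected households their own P and PC indicators, so that they are neither coded as treated nor merged with controls. Those two coefficients then estimate spillover.

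The cost is one rewritten equation and its definitions, with no new data. Trial status reports that follow-up collection had not begun at submission, so at that point the change could be made before any outcome was seen.

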### Study design

The study involves a 1:1 cluster-RCT with two intervention arms. The first intervention arm focuses on insect production. It includes agricultural training on insect farming and the provision of insect production starter kits *(Treatment P)*. The second intervention arm is focused on insect production plus insect-based food consumption. It has the same intervention components as *Treatment P* plus an additional component focused on nutrition education and insect cooking demonstrations *(Treatment PC)*. A control arm with no interventions *(Control)* serves as a comparison group for the treatments. The effectiveness of the interventions is evaluated by comparing baseline and endline data collected one year apart.

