*Secondary outcome variables*. The secondary outcome variables are: 1) Insect farming and nutrition knowledge: is measured based on simple exam-like questions relating to the content of the agricultural training and nutrition education. In the questions addressing the agricultural training, participants are asked about their knowledge regarding starting an insect farm, managing an insect farm, and harvesting insects, as well as postharvest handling practices. In the questions addressing the nutrition education, participants are asked about their awareness of the nutritional content of insects and their importance for human consumption, as well as the insect-based food products that can be prepared and consumed by humans. This way of measuring knowledge enables us to effectively capture respondents’ ability to retain knowledge and memorize specific aspects of the agricultural training and nutrition education as a result of efforts made during and after the training. Our measurement of knowledge aligns with the suggestion by Kondylis, Mueller [45], and the existing literature on the adoption of climate-smart agricultural technologies in Africa [e.g. 37, 46, 47]; 2) Dietary diversity: is measured through child dietary diversity and household dietary diversity scores [48, 49]. Both scores are based on six food groups, including meat products, eggs, vegetables and fruits, starchy foods, dairy products, and pulses, legumes and nuts. Participants are asked to report whether and how often their children have consumed foods from each food group in the past seven days for the child dietary diversity score, and in the past thirty days for the household dietary diversity score; 3) Food insecurity perception: is measured based on the food insecurity experience scale presented in Cafiero, Viviani [50]; and 4) Perceived benefits and attitudes: is measured based on different questions focusing on peoples’ willingness to take risks in general, their risk attitude towards insects farming, and their willingness to adopt insect farming as an agricultural practice. The questions are developed based on relevant literature [e.g. 51–53]. Willingness to take risks is specifically measured using a ten-point scale from 0 (unwilling to take risks) to 10 (fully prepared to take risks) [51]. The risk attitude towards insect farming and willingness to adopt insect farming are measured using a five-point scale, ranging from strongly disagree to strongly agree. Information on all the aforementioned secondary outcomes are collected during both baseline and endline surveys.

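### The basic ITT model omits baseline values that are collected for every secondary outcome, and it does not make the baseline-endline comparison described elsewhere in the protocol

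*Protocol article*

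**What the plan says.** The protocol article describes the role of baseline data in three ways.

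- **Study design** (the Abstract is similar): "The effectiveness of the interventions is evaluated by comparing baseline and endline data collected one year apart".
- **Analysis plan**: the ITT effect is estimated from Eq (1), which contains an intercept, indicators T1 and T2 for the two interventions, and an error term, with standard errors clustered by village. The impacts are taken to be β1 and β2. There is no baseline value of the outcome and no time index.
- **Analysis plan, just after Eq (1)**: "We conduct further analyses by extending Eq (1) to account for vectors of individual characteristics and other control variables, baseline and endline data". Whether this means adjustment for baseline, a change score or difference-in-differences is not said, nor which estimate leads.

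On what is collected, the Outcomes section says of knowledge, dietary diversity, food insecurity perception, and perceived benefits and attitudes: "Information on all the aforementioned secondary outcomes are collected during both baseline and endline surveys". Recruitment and randomization and Data collection both place the baseline survey before villages are assigned to arms. The draw of 15 of the 30 households in each intervention village is also made among baseline participants.

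**The concern.** Eq (1) as printed is not the comparison that the Abstract and Study design announce. If Y in Eq (1) is the endline value, baseline plays no part in the basic estimate. If the Abstract and Study design are taken literally, the estimate is a difference in changes. A third option, regressing endline on arm and the household's own baseline value (ANCOVA), is not named, although it is at least as precise as the other two under ordinary conditions.

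At stake are the width of the intervals for the secondary outcomes and clarity about which estimate is the main one. Because baseline values precede both the village randomisation and the household draw, adjusting for them adds no systematic bias.

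**Working it through.** **1. The plan's own sample size.** Inputs from Sample size: "the sample size is calculated based on a 0.8 power, 0.05 significance level and 0.06 intra-cluster correlation coefficient"; "We assume a minimum detectable effect size of 0.25 for Kenya" (the same value is used for Ghana and Uganda); and "a total of 64 clusters (villages), each with 15 participants, are needed to obtain 80% of power". Two-sided testing is assumed, and 0.25 is read as a standardised difference. For J villages in a two-arm comparison with m households each,

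Var = 4 × [ICC + (1 − ICC)/m] / J.

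With ICC = 0.06 and m = 15 the bracket is 0.06 + 0.94/15 = 0.06 + 0.0627 = 0.1227.

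- J = 64: Var = 0.00767, SE = 0.0876. The noncentral t with 62 df gives power 0.803, and 64 is the smallest even J that reaches 0.80. The plan's figure reproduces.
- J = 66 (33 per arm, as adopted): SE = 0.0862, power 0.815.

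This calculation takes no credit for baseline values.

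**2. Three estimators for an outcome measured twice.** Let r be the baseline-endline correlation, with equal variances at both rounds. Relative to endline only, the variance is 2(1 − r) for a change score and 1 − r² for ANCOVA. The documents give no r, so a range is assumed.

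| r (assumed) | Endline only, Eq (1) | Change | ANCOVA |
|---|---|---|---|
| 0.3 | 1.00 | 1.40 | 0.91 |
| 0.5 | 1.00 | 1.00 | 0.75 |
| 0.7 | 1.00 | 0.60 | 0.51 |

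The ordering does not depend on the choice of r. For 0 < r < 1, 1 − r² is below 1. It is also below 2(1 − r), since (1 − r)(1 + r) < 2(1 − r) whenever r < 1. A change score is worse than ignoring baseline when r < 0.5.

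**3. Allowing for clustering.** The table applies the same r between villages and between households within villages. With separate correlations rc (village) and ri (household),

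Var = 4 × [ICC(1 − rc²) + (1 − ICC)(1 − ri²)/m] / J.

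The village part is 0.06/0.1227 = 49% of the variance and the household part 51%. If baseline explains household-level variance only (rc = 0):

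- ri = 0.3: 0.489 + 0.511 × 0.91 = 0.954, a reduction of about 5%.
- ri = 0.5: 0.489 + 0.511 × 0.75 = 0.872, a reduction of about 13%.

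**4. What this means for precision.** The illustration uses 66 villages of 15 and a standardised difference of 0.25. The protocol does not power the secondary outcomes separately.

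| Case | Power | Effect detectable at 80% power |
|---|---|---|
| No baseline term | 0.815 | 0.245 |
| rc = ri = 0.3 | 0.849 | 0.234 |
| rc = ri = 0.5 | 0.909 | 0.212 |
| rc = 0, ri = 0.3 | 0.832 | 0.240 |
| rc = 0, ri = 0.5 | 0.864 | 0.229 |

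**5. Scale.** Data source and data collection method says that the endline questionnaire will be redesigned. A change score needs the same scale at both rounds; ANCOVA does not.

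**The case against.** The strongest reply is that the plan does use baseline. Eq (1) is presented as a starting framework, and the next sentences commit to extending it with baseline data. A reader might infer that baseline is ignored and its precision thrown away. The documents do not support that: the gain is missing from the basic estimate, not from the whole plan. A reader might also infer that the choice of estimator will stay open until outcomes are seen. That cannot be known either. An analysis plan that is not shown may fix it, and Trial status says that follow-up had not begun.

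Eq (1) is also unbiased under randomisation, and the planned power does not rely on baseline adjustment. Nothing here makes the trial invalid or underpowered.

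The size of the gain is the weakest part. It rests on an assumed r. Reading 1/(1 − r²) − 1 as 10% to 33% more sample requires the same correlation at village and household level. If only household-level variance is explained, the equivalent is 1/0.954 − 1 to 1/0.872 − 1, about 5% to 15%. Villages must be unexposed to insect farming, so farming-knowledge items may sit near the floor at baseline and correlate weakly with endline.

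What stands is a mismatch within the document itself: Eq (1) does not perform the comparison that the Abstract and Study design describe. A plainly better specification is also available from data already collected.

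**Conclusion.** The point holds as a matter of efficiency and consistency, not of bias or power. For the secondary outcomes, the estimate from Eq (1) is valid but less precise than one adjusted for the household's own baseline value. A literal change comparison would be less precise than Eq (1) if r is below 0.5.

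With r assumed at 0.3 to 0.5, adjustment lowers the variance by about 9% to 25% if r applies at both levels, or by about 5% to 13% if baseline explains household-level variance only. These figures rest on the protocol's ICC of 0.06, 15 households per village and equal variances at the two rounds. The gain could be smaller for items near the floor at baseline.

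It would be tempting to extend the argument to the primary outcomes, but the documents do not support that. Adoption is described as observed at endline. With villages unexposed to insect farming, both primary outcomes should be near zero at baseline, leaving almost nothing to adjust for. Nothing in the documents shows that other baseline items would predict them. The change is worth making, but it is not critical.

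**What to change.** - For the secondary outcomes, which are measured at both rounds, state the main specification as endline outcome on T1, T2 and the household's own baseline value, with village-clustered standard errors. The village-mean baseline may be added to capture village-level correlation, and country if the three countries are pooled.
- Keep unadjusted Eq (1) as a sensitivity analysis.
- Reword the Abstract and Study design so that they describe this analysis, and say in the Analysis plan that Y is the endline value.

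The cost is a few lines of text. The baseline data are already collected and, with follow-up not begun at submission, the choice can be fixed before endline outcomes are seen.
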